## Rationale

This will be the first cluster RCT to measure the effect of a package combining economic support and a community component to prevent adolescent childbearing in a LMIC. A number of studies have found that economic support to girls and/or their families can increase school enrolment and attendance [38-41], and a couple of trials have found effects on postponement of childbearing and marriage [18, 19, 25]. Increased schooling among adolescent girls is likely to empower them economically [42] and cognitively, and to enable them to better protect the health of their children [11] and themselves. A meta-analysis has found that an increase of 1 year in the education of women is associated with 6.5-9.9% lower under five mortality in LMICs [43]. Other studies indicate that widespread myths and negative social norms are barriers to adolescent girls using modern contraceptives, thus contributing to high rates of early pregnancy. However, there is little robust research from Africa on how sexual and reproductive health programmes can be delivered in a way that actually affects early marriage and pregnancy rates. Delaying first marriage is likely to contribute to delayed age at first pregnancy, and a lower adolescent pregnancy rate is likely to reduce morbidity and mortality among women [1] and children [2, 5]. The need to find ways to prevent early marriage and pregnancy are high on the political agenda in Zambia.

## Trial objectives

### *Primary objectives:*

1. To measure the effectiveness and cost-benefit of providing economic support to girls and their families on adolescent childbearing and grade 9 completion in a Zambian context
2. To measure whether combining economic support to girls and their families with a community intervention targeting social norms and normative, behavioural and control beliefs regarding education and sexual and reproductive health, is more effective and cost-beneficial in reducing adolescent childbearing and increasing grade 9 completion than economic support alone.

### *Secondary objectives:*

1. To measure the effectiveness of economic support alone and a combined intervention on early marriage among adolescent girls
2. To measure the effectiveness of economic support alone and a combined intervention on secondary school enrolment, school attendance, dropout, exam scores and employment among adolescent girls
3. To measure the impact of economic support alone and a combined intervention on the socioeconomic distribution of adolescent childbearing and marriage
4. To measure the effectiveness of economic support alone and a combined intervention on changing normative beliefs related to girls’ education, early marriage, modern contraceptive use, and adolescent pregnancy.
5. To measure the effectiveness of economic support alone and a combined intervention on knowledge about sexual and reproductive health, use of modern contraceptives and behavioural, normative and control beliefs related to modern contraceptives, and self-reported sexual risk behaviour among adolescent girls

## Hypotheses

### Primary

1. The economic support will reduce the incidence of births before girls’ 18th birthday by at least 25% and increase the proportion who completes grade 9 by 15%;
2. The combined intervention (with economic support and the community component) will reduce the incidence of births within 8 months of the end of the intervention period and the incidence of births before girls’ 18th birthday by at least 40%, and increase the proportion who completes grade 9 by 26.5%.

### Secondary

1. Both interventions will significantly reduce school dropout, and increase secondary school enrolment, school attendance, exam scores and employment among adolescent girls.
2. Both interventions will significantly reduce early marriage, sexual risk behaviour and increase modern contraceptive use since the economic component will increase girls’ motivation to avoid pregnancy, and the community component will change behavioural and normative beliefs concerning contraceptive use.

# 2. TRIAL METHODOLOGY

## Trial design

The intervention packages will be examined in a cluster randomized controlled trial with two intervention arms and one control arm.

## Study setting

The trial will be conducted in twelve districts in Zambia: Monze, Mazabuka, Chikankata, Kapiri Mposhi, Kabwe, Chisamba, Chibombo, Mkushi, Luano, Pemba, Kalomo and Choma. These districts have been selected as they have medium school drop-out rates, and adolescent marriage and childbearing is common (unpublished data from 2010 ZCPH).

## Randomization units

#### A randomization unit or cluster will be a school offering grades 1-9. All the schools should be accessible from the District Educational Board Secretary’s (DEBS) office all year round and should have reasonably good mobile network coverage. Clusters will be purposively selected to ensure sufficient corridors (i.e. areas that are not included) between them in order to minimize the risk of contamination.

## Participant population

#### The participant population will be girls enrolled in grade 7 (average age approx. 14 years) in 2016 in rural basic schools in the twelve study districts.

## Eligibility criteria

All girls enrolled in grade 7 in the included schools will be eligible to participate, including those who are already married or have children. Girls without a parent or legal guardian living in the household will also be eligible to participate if the headmaster of their school or the headman of the village gives consent. There will be no age restriction.

Girls who drop out of school after they have been recruited will continue to be part of the trial.

## Participant retention

We will invest substantial resources to minimize bias and potential confounding by endeavouring to ensure more than 90% follow-up of participants. We will also invest resources to ensure that the follow-up percentage does not differ more than 5% between the three trial arms. The participants will receive a letter with the telephone numbers to the study’s main office and local trial supervisor so that they can inform project staff about any changes in their place of residence or primary contact telephone number. In addition, contact details will be updated by phone twice per year. As a token of appreciation of their time, the participants will be given a small compensation (of approx. 3-4 USD) when they respond to a few questions about current residence, school enrolment, marital status and childbirths, and when they participate in baseline and the final-up surveys. (Girls in the intervention arms will not receive compensation for answering questions during the follow-up contacts at the same time as they are receiving economic support, only after this support has come to an end. If they do not respond to questions during the intervention period, the economic support will be stopped.) If participants cannot be interviewed face-to-face, attempts to interview them by phone will be made. In case their phone number changes, relatives or neighbours we have recorded the contact details of will be asked to provide current contact details for girls. Girls who consent to participate in the trial but refuse to receive the intervention, will still be followed-up.

If we experience substantial post-randomization drop out, we will introduce additional incentives to keep participants in the trial.

## Community sensitisation

An important key to the success of the recruitment process and the intervention packages is the support from traditional leaders, other community leaders and the wider community. To achieve community acceptance chiefs, headmen, religious and informal leaders, headmasters and parent-teacher association members will be oriented and asked to support the trial activities before the recruitment is initiated. Local radio will also be used for community sensitization. If overall >15% of the families/girls in consenting schools decline participation, measures will be made to reduce refusals to participate to below 10%. Any individual school in which >20**%** of the girls do not consent to participate will not be included in the study.

After randomization, further consultative meetings will be held in all the trial arms for the same key groups, and the headmen and headmasters in the intervention areas will be engaged in the promotion of both intervention packages and in the implementation of the community component.

## Interventions

### The interventions will be launched in September 2016 and last for 28 months, until November 2018 (end of the academic year when the girls who attend school are expected to complete grade 9). In the control arm, girls will be offered some writing materials (exercise books, pencils and pens) as an incentive to participate. This is not likely to be sufficient to have any effect on the primary or secondary outcomes. Apart from this, only standard school and health services will be offered. The interventions will be delivered through personnel in the school and the health system to facilitate potential scale-up in Zambia and similar contexts.

### *‘Economic support’ arm*

In this intervention arm girls and their parents/guardians will be offered economic support, which will consist of UCTs for the girl (ZMW 30/month) and her parents/guardians (ZMW 350/year) and payment of school fees for girls who enrol in grade 8 and 9. The UCT amount corresponds to the approximately K70 provided monthly (in 2014) in the government’s Child Grant scheme for families with children under 5 [44], and it is only slightly higher than the 8 USD provided per month to poor households through the Inclusive Model [37]. Thus this amount is likely to be within the range that the government would consider if it were to implement a cash transfer programme for families with adolescent girls. This is estimated to be sufficient to pay for a school uniform and shoes, a school bag, books and writing materials, and the combination of the UCT and payment of school fees would thus make schooling free of cost for the family of an adolescent girl.

The money for the girls and the guardians will be disbursed by a cash transfer committee consisting of a teacher and two parents from the Parent-Teacher Association (PTA) committee. At least two of the cash transfer committee members will be present during disbursement to witness that the right persons receive the cash. If the girl moves, the money will be transferred via a mobile bulk transfer system. This implies that the recipient of the cash transfer must be a person above age 16 with a registered sim card. For girls who are younger than 16 years, one of the parents/guardians will be selected as the recipient of the parent/guardian cash transfer. Every month this parent/guardian will receive a text message with a unique reference number from the mobile transfer operator and this code can be used to obtain cash at the nearest agent. The parents/guardians will be informed that they should be accompanied by the girl when collecting the cash. Girls who are aged 16 or older and who have a registered sim card can receive the monthly cash transfer themselves. To ensure that all the recipients receive what they will be entitled to, questions will be asked in every follow-up contact about how much they have received, and all participants will be encouraged to contact the study team if they do not receive the amount they believe they are entitled to. The economic support will be stopped for girls who do not respond to questions in the follow-up contacts.

The payment of school fees will be made directly to the school account for girls who get a place in grade 8 and 9. There will be no age limit for receiving the economic support for those girls who are in school, but the economic support will stop after the 18^th^ birthday for girls who drop out of school.

The support package targets the key actors in the decisions leading to early pregnancy and marriage. UCTs target the poverty dimension, by making it less urgent for the parents/guardians that the girl gets married and less urgent for the girl to receive gifts from a boy-friend. The payment of school fees (combined with the UCT) targets the school drop-out dimension, with the combination removing economic barriers to the girl continuing in school. Staying in school in turn reduces the likelihood that she becomes married or pregnant. In sum, both these effects may reduce early pregnancies.

### *‘Combined intervention’ arm*

The second intervention arm will combine the economic support component with a community-oriented strategy, aiming to reduce early marriage and childbearing through (1) community and parent meetings promoting supportive social norms around education for girls and postponement of early marriage and early childbearing; and 2) establishment or strengthening of existing youth clubs in order to increase knowledge of sexual and reproductive health (SRH), including modern contraceptives, and change behavioural and control beliefs relating to contraceptive use among in- and out-of school adolescent girls and boys. We expect that the combination of these strategies will reduce early sexual activity and increase use of modern contraceptives and thus reduce pregnancy rates among adolescent girls, as well as further reducing school-dropout and delaying age of marriage compared to providing economic support alone, thus affecting childbearing rates also indirectly.

The SRH education will be delivered as part of a youth club that will have meetings twice per month in the school or community. Girls participating in the trial and boys who attend the same grades as these girls will be invited to participate in a youth club, and they will all be allowed to continue in the youth club even if they drop out/quit school. The meetings will include interactive discussions on education and employment opportunities, early marriage, the risks of early pregnancy, misconceptions around modern contraceptives, and skills training, e.g. negotiation of modern contraceptives use with a sexual partner. We will base the content of the meetings on the “Tuko Pamoja. Adolescent Reproductive Health and Life Skills Curriculum” developed by the Kenya Adolescent Reproductive Health Program, Program for Appropriate Technology in Health (PATH), and the Population Council [45], with some adaptations to fit the purpose of this trial. (The curriculum will be called “Tuli Antoomwe” in Tonga and “Tuli Pamo” in Bemba.) This interactive curriculum gives detailed descriptions of the content and activities of each meeting. We will add some sessions (e.g. on the value of education, initiation rites, early marriage, school re-entry and SRH rights). The sessions we have prepared was reviewed by experts from the Ministry of Health in Zambia to ensure that they were based on sound pedagogical principles and that the content is in line with the Zambian framework for Comprehensive SRH education. Appendix 2 provides a list of all the sessions that are planned. Some sessions may be repeated or extended over several meetings. Girls and boys will be split in separate groups when sensitive issues are discussed. In some meetings there will also be time for games and sports. Refreshments will be provided in the meetings to attract girls and boys to turn up.

To run the youth clubs, we will test a model where a community health assistant (CHAs)^[[4]](#footnote-5)^ or community workers (CHW) is linked with a teacher from the school in the cluster to form a community team. This team will collaborate in providing comprehensive SRH education to girls and boys both in- and out-of school, and the CHA/CHW and the teacher will take the lead role for some sessions each. The trial supervisor will supervise the youth club activities. A meeting will be held once a year to inform parents about the content of the future youth club sessions.

For each combined intervention cluster, two young (<20 years) unmarried women from the local community will be selected as youth peer educators. These youth peer educators should be girls who are well liked and respected among the girls in grade 7. The role of these peer educators will be to mobilize girls and boys to come to youth club meetings.

Meetings with the community at large will be organized twice per term by the trial supervisor in collaboration with headmen and the teacher and CHA/CHW in the community team. These meetings and the parent meetings will be conducted using a dialogue approach [49]. The discussion in such meetings should be free and democratic, although the persons leading the meetings may gently guide the discussion in a certain direction. Group discussions may contribute to behaviour change because the conversation can change people’s understanding of what is acceptable or desirable (i.e. their normative beliefs) and thus the social norms in the community. The hope is that the community members will agree on some action points related to the topic discussed since people often feel committed by group decisions if they perceive that they arrived at the decision to change a behaviour voluntarily [50]. If group decisions are made, these will be discussed again in ensuing meetings.

In community- and youth club meetings, films or role plays presenting simple messages will be used to start discussions. Two films (of 10-15 minutes duration each) have been produced. The two films that have been produced focus on early marriage, early pregnancy and the value of education. The films are drama-based and convey stories of girls with readily recognizable lives (girls in and out of school, girls with early and later pregnancies, unmarried girls, girls within early marital unions etc). A key notion is that the films should not reveal strong negative sentiments or disgust for certain life trajectories, but present messages in a locally adapted, respectful and nuanced way that calls for reflection and opens up for discussion. The production of the films has been subcontracted to Kula Music Studio Ltd, a Zambia-based non-profit, non-religious organization, which has previously made films and documentaries on reproductive health topics, and also has expertise in scripting, filming, and editing.

Before the launch of the combined intervention, a comprehensive 5 day training of the selected teachers, CHAs/CHWs, and the trial supervisor will be conducted and will include the SRH curriculum, facilitation techniques and community mobilization. The youth peer educators will be given 3 days training in peer counselling and reproductive health. The trainings will be carried out by the research team with some support from subcontracted persons from NGOs carrying out similar programmes.

## Outcomes

### *Primary outcomes:*

- incidence of births within 8 months of the end of the intervention period;
- incidence of births before girls’ 18^th^ birthday;
- proportion of girls who sit for grade 9 exam.

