## Sample size

The sample size is estimated based on the primary outcomes “incidence of births within 8 months of the end of the intervention period” (average age expected to be 17.5 years), “incidence of births before girls’ 18^th^ birthday” and “proportion of girls who sit for grade 9 exam”. We used the 2010 census age-specific estimates of the proportions of 17 and 18 year old girls who ever given birth in the study districts to estimate the proportions in the control arm. The census indicates that 22% of 17 year old and 35% of 18 year old girls in the study districts had ever given birth. Based on this we assume that 27% of girls in the control arm will have given birth before their 18^th^ birthday.

All estimates below have been increased with 10% to compensate for a possible loss to follow up. The sample-size for this cluster-randomized controlled trial was calculated using PASS 14 (NCSS Statistical Software, Utah, US).

*Assumptions for sample size required to measure the primary outcome “birth within 8 months of the end of the intervention period” (*when the average age will be 17.1 years)

| **Parameter** | **Assumed level** | **Comment** |
| --- | --- | --- |
| Incidence of births in control group | 0.06 | Eight months after the end of the intervention period the girls will be on average 17.1 years and we assume that 15% of them will have given birth. This corresponds to an average incidence rate of (15%-3%)/2= 6% over this 2 year period. |
| Effectiveness of combined intervention vs control | -40% | i.e. incidence in combined intervention arm assumed to be 0.036 |
| Cluster size | 28 | See assumptions for the outcome “incidence of births before girls’ 18th birthday” |
| Person years per cluster | 56 | If 28 participants are followed up for 2 years, there will be 56 person years |
| Coefficient of variation (k) | 0.2 | The ICC was 0.00737 for “ever pregnant” after cash transfer trial in Malawi. This corresponds to k=0.20 when the total proportion who have given birth by this time is 0.15 |
| Z_1_ (acceptable alpha error level) | 1.96 |  |
| Power for comparison of combined intervention vs control | 90% | We need 36 combined clusters vs 36 control clusters to have 90% power detect the assumed difference. The PASS function for proportions indicates that with 63 combined clusters, we will have >90% power with 30 control clusters. |
|  |  |  |

*Assumptions for sample size required to measure the primary outcome “birth before 18^th^ birthday”*

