| **Parameter** | **Assumed level** | **Comment** |
| --- | --- | --- |
| Incidence of births before girls’ 18th birthday | 0.08 | We assume that 27% of girls in the control arm will have given birth before their 18th birthday. This corresponds to an average incidence rate of (27%-3%)=8% per year over the average 3 year period (from the time the average age is 15). |
| Effectiveness (i.e. (1-RR)×100 of economic intervention vs control | -25% | I.e. the incidence in economic intervention arm assumed to be 0.06 |
| Effectiveness of combined intervention vs control | -40% | i.e. the incidence in combined intervention arm assumed to be 0.048 |
| Effectiveness of combined intervention vs economic intervention | -20% | The combined intervention will offer [1-(0.0.048/0.06)], i.e. 20% more relative protection than the economic intervention alone. |
| Cluster size | 28 | Average number of girls in grade 7 in the selected schools is 31. If we assume that up to 10% may be lost to follow up by the time of measuring the outcome, the average cluster size will be 28 |
| Person years per cluster | 84 | If 28 participants are followed up for 3 years on average, person years per cluster are 84. |
| Coefficient of variation (k) | 0.15 | The ICC was 0.00737 for “ever pregnant” after intervention period in cash transfer trial in Malawi (estimate obtained from [name]). This corresponds to k=0.15 when the total proportion who have given birth by this time is 0.27 [51]. |
| Z_1_ (acceptable alpha error level) | 1.96 |  |
| Power for comparison of economic intervention vs combined intervention | 70% | We need 63 clusters in each of the intervention arms to have 70% power to detect the assumed difference |
| Power for comparison of economic intervention vs control | 80% | We need 39 clusters in each arm to have 80% power to detect the assumed difference. The PASS power calculator for incidence rates does not allow for unequal trial arms, but the PASS function for proportions indicates that 63 economic and 31 control will give slightly higher power^[[5]](#endnote-2)^ |
| Power for comparison of combined intervention vs control | >95% | We need 23 clusters in each arm to have 95% power to detect the assumed difference. |
|  |  |  |

*Assumptions for sample size required to measure the primary outcome ‘proportion of girls who sit for grade 9 exam’*

| **Parameter** | **Assumed level** | **Comment** |
| --- | --- | --- |

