## Statistical methods

The outcomes will be captured in binary, continuous or a time-to-event variables. Continuous variables that are right skewed will be log-transformed to obtained more symmetrical distributions. We will correspondingly employ Poisson regression or General linear models (GLM) of the binomial family with a log link (estimating risk ratios or RRs) and identity link (estimating absolute risk reduction), linear regression (estimating average effect or mean increase or decrease) or survival analysis using Cox regression. Each method will take account of the design effect of the clustering.

The data will be analysed with Stata (Stata Corporation, TX, USA) statistical software. We will compare outcomes between the three arms: the economic arm vs. the control arm, the combined arm vs the control arm, and the economic arm vs the combined intervention arm. Analyses will be by intention-to-treat (ITT), that is all participants, irrespective of whether they actually agree to the intervention allocated to them, will be included in the analysis according to the intervention arm the cluster they live in was allocated to. The Intracluster correlation (ICC) will be reported for all primary and secondary outcomes.

The primary outcomes will be measured in the final survey in February 2020 based on the participants’ responses to the questions “Have you ever given birth?” and “If yes, on which date and which year did you give birth?”. Reported childbearing before July 2019 will be recorded as “birth 8 months after end of the intervention period”. Girls who report a date of childbearing preceding their 18^th^ birthday, will be recorded as having “birth before 18^th^ birthday”. Girls who are married at the start of the intervention, will be excluded from the analysis of proportion of girls ever married/cohabiting before their 16^th^ or 18th birthday.

Descriptive statistics, such as means or medians and standard deviation or interquartile range will be used to describe continuous variables (the choice depending on the distributions). For categorical variables, frequencies and percentages will be calculated.

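### The two primary birth outcomes have an end but no start, so births already conceived at allocation count as events, dilute the rate ratios and cost power that the sizing does not allow for

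*Protocol*

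**What the plan says.** Under Outcomes, the first primary outcome is the "incidence of births within 8 months of the end of the intervention period" and the second is the incidence of births before the 18th birthday. Neither has a start date.

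Statistical methods turns these into counting rules. Both rest on a survey question that begins "Have you ever given birth", plus the date of birth. For the first outcome, "Reported childbearing before July 2019 will be recorded as" an event. For the second, the rule begins "Girls who report a date of childbearing preceding their 18" (th birthday) and again sets only an upper limit.

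Girls who already have children are eligible, and Eligibility criteria states no exclusion for pregnancy. The one baseline exclusion concerns marriage: "Girls who are married at the start of the intervention, will be excluded from the analysis of proportion of girls ever married/cohabiting".

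On timing, Randomization and blinding/masking places allocation in July 2016. Interventions says "The interventions will be launched in September 2016" and ends them in November 2018, so 8 months later is July 2019.

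Sample size works with limited windows. For the first outcome the control rate is ("15%-3%)/2= 6% over this 2 year period". For the second it is 8% per year "over the average 3 year period (from the time the average age is 15").

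**The concern.** Neither package could have prevented a conception that predates allocation. Counting nine months from July 2016, births up to about April 2017 are mostly of that kind. Starting the count on the randomisation date would not remove them.

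Randomisation spreads these births evenly over the arms, so they add about the same number of events to each and pull the ratio towards 1. The Hypotheses section states its targets as relative reductions of 25% and 40%, so this is the scale that suffers.

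The sizing does not carry this load. Two years ending in July 2019 begin in July 2017, about 10 months after launch, and 3% is subtracted for births before the window. The stated power therefore belongs to a narrower set of births than the one the counting rule collects. The tightest comparison, combined v economic, is planned at only 70% and answers the second primary objective.

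**Working it through.** **1. Reproducing the plan's figures.** Clusters per arm for comparing incidence rates:

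c = 1 + (1.96 + z)² × [(λ0 + λ1)/y + k²(λ0² + λ1²)] / (λ0 − λ1)²

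All inputs are from Sample size.

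- First outcome, combined v control, 90% power (λ 0.06 v 0.036, y = 56, k = 0.20): 1 + 10.51 × (0.001714 + 0.000196)/0.000576 = 35.8, so 36. Stated: 36.
- Before 18, economic v control, 80% (0.08 v 0.06, y = 84, k = 0.15): 38.1, so 39. Stated: 39.
- Before 18, combined v control, 95% (0.08 v 0.048): 22.8, so 23. Stated: 23.
- Before 18, combined v economic, 70% (0.06 v 0.048): 61.8, so 62. Stated: 63.

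The plan's figures are sound for the windows they assume.

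**2. Power at the planned 63/63/31 clusters.**

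Power = Φ(|λ0 − λ1|/√v − 1.96), with v = (λ0/y + k²λ0²)/(c0 − 1) + (λ1/y + k²λ1²)/(c1 − 1)

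In the plan's own windows this gives 91.6% (first outcome, combined v control), 81.2% (before 18, economic v control), 70.8% (before 18, combined v economic) and 99.7% (before 18, combined v control).

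**3. Adding the unpreventable births.** Let q be the share of girls per arm with a counted birth from a pregnancy that could not have been prevented. The protocol does not give q. Its own 3%, read here as girls who had given birth by about age 15, is a rough ceiling and also includes births before baseline.

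Control-arm births in the plan's windows are 15% − 3% = 12% (first outcome) and 27% − 3% = 24% (before 18). The diluted ratios are:

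- First outcome: (q + 0.12 × 0.60)/(q + 0.12)
- Before 18, economic v control: (q + 0.24 × 0.75)/(q + 0.24)

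Risk time is lengthened by 10 months (to 34/12 and 3 + 10/12 years), with k unchanged.

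| q | First outcome: RR, power | Before 18, economic v control: RR, power | Before 18, combined v economic: RR, power |
|---|---|---|---|
| 0 | 0.600, 91.6% | 0.750, 81.2% | 0.800, 70.8% |
| 0.5% | 0.616, 90.2% | 0.755, 80.3% | 0.805, 69.4% |
| 1% | 0.631, 88.7% | 0.760, 79.3% | 0.811, 68.0% |
| 2% | 0.657, 85.7% | 0.769, 77.4% | 0.820, 65.3% |
| 3% | 0.680, 82.6% | 0.778, 75.5% | 0.829, 62.7% |

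For q of 0.5-3%, these births are 4-20% of control events on the first outcome and 2-11% before 18. Combined v control before 18 moves from RR 0.60 to at most 0.64, with power still above 99%.

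**4. Absolute scale.** On the first outcome the difference in proportions is (q + 0.12) − (q + 0.072) = 0.048 whatever q is.

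**5. Cross-check on q.** Births were interpolated through the census figures (11% at 16, 22% at 17, 35% at 18), with mean age 14.1 in July 2016 and SD 1.0-1.8 years assumed. Births in the first nine months after allocation are then 11-15% of those to July 2019 and 7-9% of those before 18. Solving q/(q + 0.12) and q/(q + 0.24) for these shares gives q of about 1.5-2.4%. The same model puts the share at 20-23% for births before 16.

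**The case against.** *Pregnancies at allocation are balanced by randomisation, so nothing is biased.* This stands. A reader might infer a biased or invalid test, and the documents do not support that. Counting all births after allocation is an ordinary intention-to-treat effect. The loss is in the ratio and in power, and the protocol also plans absolute differences, which barely move.

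*The sizing was not deliberately lagged for gestation.* This also stands. It is tempting to read the 8-month rule and the age-15 start as gestation allowances, but the protocol explains neither in that way. The mid-2017 start also depends on which age is used. Sample size gives both 17.1 and 17.5 years as the average age for the same outcome. From 17.1, average age 15 falls about 2.1 years before July 2019, around June 2017. From 17.5 it falls in about January 2017, some four months after launch. What remains is that the sizing window is shorter than the counting rule.

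*Early births are probably rarer here than in the census.* This is fair. All participants are enrolled in grade 7 at entry, and the protocol reports 36% v 5% childbearing at age 17 for out-of-school v in-school rural girls. The 11% at age 16 also comes from only three districts. This argues for the lower rows of q but does not make the effect vanish.

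*The start of risk time belongs in the analysis plan.* This stands in part. An analysis plan that is not shown may settle it. But the protocol itself fixes a counting rule with no lower limit and sizes on a different window, so its own sections need to agree.

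*Removing early births conditions on something decided after allocation.* This is partly right. Miscarriage and termination are listed outcomes, so whether an existing pregnancy becomes a birth is settled after allocation. The exclusion is only approximately a pre-allocation one.

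**Conclusion.** The point holds as a loss of ratio effect and power. It does not show an invalid analysis or a wrong sample-size figure. Followed literally, the counting rules include births from pregnancies that predate allocation, and the sizing does not.

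If 1-3% of girls per arm are affected, a true 40% reduction on the first outcome reads as about 37-32%, and a true 25% reduction before 18 as about 24-22%. Economic v control before 18 drops just below its stated 80% power, and combined v economic drops further below 70%. Combined v control before 18 is hardly touched.

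These sizes rest on the assumed q, on equal q in all arms, and on unchanged between-cluster variation. At q = 0.5% the loss is about 1 percentage point of power. The effect is modest, but it can be recovered cheaply.

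**What to change.** - State that risk time for both primary birth outcomes, and for birth before 16, starts a fixed gestation interval of about 9 months after the cluster's randomisation date (about April 2017), identically in all arms.
- Treat girls with an earlier birth as parous or pregnant at baseline and outside the first-birth risk set.
- Make Sample size and Statistical methods use the same window, and reconcile the 17.1 and 17.5 year figures. April 2017 to July 2019 is 2.25 years, so the first outcome's person-years per cluster would be 28 × 2.25 = 63 instead of 56, with the control rate restated to match. Average age at the start would be 17.1 − 2.25 = 14.85 or 17.5 − 2.25 = 15.25, close to the age 15 already assumed.
- Keep all births since randomisation as a prespecified sensitivity analysis.

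The cost is wording and a restated calculation, because birth dates are collected and randomisation dates are known. The downsides are slightly fewer events, a few preterm births conceived after allocation being set aside, and an exclusion that is only approximately pre-allocation because some existing pregnancies end in loss or termination. Pregnancies conceived between July and the September 2016 launch would still count. The sensitivity analysis shows how much the choice of start matters.
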